## Objective

To study whether expectant management is an alternative to treatment with systemic MTX in a single dose im regimen in women with an EP and low but plateauing serum hCG concentrations in terms of tubal rupture, future pregnancy, health related quality of life and costs.

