### Follow up

#### Short term follow up

In both groups weekly serum hCG measurements will be performed until serum hCG is no longer detectable. Serum hCG concentrations are expressed in IU/L (conversion factor to SI unit, 1.00 according to the World Health Organization Third International Standard 75/537). Seven days after a MTX injection liver and renal function and full blood count are checked. Complications will be registered in the Case Record Form.

In patients treated expectantly, treatment with systemic MTX (single shot 1 mg/kg im) is started whenever at any of the weekly follow up visits the serum hCG concentration has risen > 15% of the prior value. Expectant management is continued if the serum hCG concentration falls by > 15% of the prior value [20]. In case of a persistent plateauing serum hCG concentration, defined as < 15% fall or < 15% rise, the serum hCG concentration is assessed after 48 hours to ensure it is not increasing. If it is increasing as described above, treatment with systemic MTX as described above is installed. Whenever hemodynamic instability and/or clinical signs of tubal rupture (i.e., increasing abdominal pain in combination with falling haemoglobin level and signs of intra abdominal haemorrhage on TVS) occur, surgical intervention is carried out.

In patients treated with MTX, an additional MTX injection is given in case the serum hCG concentration on day 7 has declined <15% of the initial value on day 1 (start of treatment) [11]. If the serum hCG concentration fails to fall by at least 15% during any successive week of follow-up, repeated doses of MTX are given, with a maximum of three additional injections [21]. In case of hemodynamic instability and/or signs of tubal rupture, i.e., increasing abdominal pain in combination with falling haemoglobin level and signs of intra abdominal haemorrhage on TVS, or whenever more than four MTX injections are required, surgical treatment is indicated.

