#### Secondary outcome measures

Secondary outcome measures are (re)interventions (additional MTX injections or surgical procedures for persistent trophoblast and/or clinical signs), treatment complications, health related quality of life, financial costs, and future fertility. Moreover, patients' preferences will also be assessed.

Health related quality of life is assessed by standard self administered psychometric questionnaires with established viability and reliability at different time points, i.e. before randomisation, after one week, four weeks and three months.

Costs are expressed in direct costs with data on costs and used resources in the participating centres.

Future fertility is defined as time to the occurrence of a spontaneous viable IUP. A viable IUP is defined as the presence of fetal cardiac activity at a gestational age of ≥ 12 weeks. If an IUP does not occur, follow-up ends at the last consultation. In addition to IUP, repeat EP is also assessed. The date of occurrence of an EP will be determined from the first day of the last menstrual period.

Patients' preferences are assessed by an online questionnaire using a discrete choice experiment (DCE) based on characteristics of both interventions and will be compared with a control group, recruited among women visiting the infertility clinics of the participating hospitals.

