#### Analysis

Data analysis is performed according to the intention to treat principle.

Short term outcome measures are compared by calculating relative risks and their 95% confidence intervals. Future fertility is assessed by life table analysis. Kaplan-Meier curves are constructed, estimating the cumulative probability of time to spontaneous IUP and repeat EP. If a spontaneous viable IUP does not occur, follow up ends at the last date of consultation, or at the start of in vitro fertilisation (IVF) treatment or the date of tubal surgery. Spontaneous conceptions that occur after failed IVF treatment will be registered. The log-rank test is used to test differences between the Kaplan-Meier curves for statistical significance. The differences between both treatment modalities are expressed as a fecundity rate ratio with 95% confidence interval, calculated through Cox proportional hazard analysis.

Changes in health related quality of life over time, and differences between the two groups will be measured using analysis of variance.

Depending on differences of equivalence between the strategies, the economic evaluation will be a cost-effectiveness analysis or a cost-minimisation analysis.

Patient's preferences are analysed by differences in outcome of the DCE.

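### Fertility follow-up stops at tubal surgery without excepting surgery for the index pregnancy; read plainly, this is informative censoring in a secondary outcome, of unknown and probably small size

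*Protocol article*

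**What the plan says.** Future pregnancy is part of the stated aim. The Objective asks whether expectant management is an alternative to methotrexate (MTX) "in terms of tubal rupture, future pregnancy, health related quality of life and costs".

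The Secondary outcome measures section defines the outcome: "Future fertility is defined as time to the occurrence of a spontaneous viable IUP". It gives one end-of-follow-up rule: "If an IUP does not occur, follow-up ends at the last consultation".

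The Analysis section opens with "Data analysis is performed according to the intention to treat principle". For women without a spontaneous viable IUP it then adds two further stops to the last consultation: "or at the start of in vitro fertilisation (IVF) treatment or the date of tubal surgery". Arms are compared by Kaplan-Meier curves and a log-rank test, with the difference "expressed as a fecundity rate ratio with 95% confidence interval, calculated through Cox proportional hazard analysis". Spontaneous conceptions after failed IVF are to be registered. Nothing similar is said about conceptions after tubal surgery.

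The Short term follow up section says when surgery happens. In the expectant arm the trigger begins "Whenever hemodynamic instability and/or clinical signs of tubal rupture". The MTX arm has the same triggers and one more: "whenever more than four MTX injections are required, surgical treatment is indicated". Surgical procedures are also counted among the (re)interventions, a secondary outcome.

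**The concern.** Surgery for the index pregnancy comes after randomisation and depends on how the allocated strategy worked out. Kaplan-Meier and Cox methods are valid only if a censored woman's later prospects match those of women still at risk. Tubal surgery may well change the chance of spontaneous conception, so censoring on it is informative.

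Index surgery would fall in the first weeks. Such a woman would add almost no fertility time, and the analysis would in effect impute to her the experience of women who were not operated on. That is a comparison of arms as if surgery did not occur. Intention to treat asks something else: what happens to all women allocated to each strategy, whatever follows.

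At stake is one pathway that the Objective makes relevant, from rupture through surgery to later pregnancy. If the arms differ along it, the fecundity rate ratio would understate the difference.

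**Working it through.** **The plan's own figure.** No planning figure exists for fertility. The only sample-size figure is 36 per group for the primary outcome (60% v 90%, power 80%, 5% level). It reproduces: two-sided Fisher exact power at 36 per group is 80.0% (normal-approximation formula: 32 without and 38 with continuity correction). It serves here only as the denominator of 36 per arm.

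**The passages side by side.**

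| Item | Secondary outcome measures | Analysis |
|---|---|---|
| Stop at last consultation | yes | yes |
| Stop when IVF begins | not mentioned | yes |
| Stop at tubal surgery | not mentioned | yes, without restriction |

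The term used for the surgery stop is not defined, and the text does not limit it to surgery unrelated to the index pregnancy.

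**Size: inputs.** Follow-up of 24 months is from Long term follow up. Everything else is an assumption, because the documents give no surgery or conception rates:
- monthly rate of spontaneous viable IUP without surgery, λ = 0.03 or 0.06;
- rate after surgery multiplied by h = 0.5 or 0.25;
- share operated on early, s = 10% v 3% or 20% v 5% (expectant v MTX);
- no other difference between the arms.

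**Formulas.** Without surgery, P0 = 1 − exp(−24λ). After surgery, Ph = 1 − exp(−24λh).
- Follow-up ended at early surgery: both arms show P0, and the rate ratio is about 1.
- All women kept: P = (1 − s)P0 + s·Ph. The difference between arms is (sE − sM)(P0 − Ph).
- Approximate rate ratio: ln(1 − PE) / ln(1 − PM), the ratio of 24-month cumulative hazards.

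**Numbers.** At λ = 0.06, P0 = 1 − exp(−1.44) = 76.3%; Ph = 51.3% (h = 0.5) or 30.2% (h = 0.25). At λ = 0.03, P0 = 1 − exp(−0.72) = 51.3%; Ph = 30.2% or 16.5%.

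| λ | h | Surgery, expectant v MTX | Censored, both arms | All women kept | Hidden difference (points) | Ratio, all kept |
|---|---|---|---|---|---|---|
| 0.03 | 0.5 | 10% v 3% | 51.3% | 49.2% v 50.7% | 1.5 | 0.96 |
| 0.06 | 0.5 | 10% v 3% | 76.3% | 73.8% v 75.6% | 1.7 | 0.95 |
| 0.03 | 0.5 | 20% v 5% | 51.3% | 47.1% v 50.3% | 3.2 | 0.91 |
| 0.06 | 0.5 | 20% v 5% | 76.3% | 71.3% v 75.1% | 3.7 | 0.90 |
| 0.03 | 0.25 | 20% v 5% | 51.3% | 44.4% v 49.6% | 5.2 | 0.86 |
| 0.06 | 0.25 | 20% v 5% | 76.3% | 67.1% v 74.0% | 6.9 | 0.83 |

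Cox ratios from simulation at λ = 0.06 agree to within 0.01 to 0.02. They are 0.99 to 1.00 when operated women are censored at two weeks.

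**Equal surgery rates.** With 10% operated on in both arms, λ = 0.06 and h = 0.5, the ratio is 1.00 either way, but both censored curves are too high by 0.10 × (76.3 − 51.3) = 2.5 points.

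**Against sampling error.** Take the fourth row, with all 36 women per arm assumed to be trying to conceive. Expected pregnancies are 36 × 0.713 = 25.7 and 36 × 0.751 = 27.0. The standard error of the log rate ratio is about √(1/25.7 + 1/27.0) = 0.28, so the 95% interval runs from the estimate divided by 1.72 to the estimate multiplied by 1.72. A shift from 1.00 to 0.90 is far inside that. The hidden difference there is 0.037 × 36, or about 1.3 women.

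**The case against.** The strongest reply concerns meaning. The phrase for tubal surgery occurs only in the fertility rule, next to IVF, and rescue surgery for the index pregnancy is named in other words elsewhere. The authors may have meant later surgery, after which a conception would no longer be called spontaneous. Then nobody is censored in the first weeks, and the figures above, which model early surgery only, do not apply. This stands as a possible reading, but the text does not state it. Later surgery for a repeat ectopic pregnancy would also be informative, because it may mark women with damaged tubes. An undefined censoring event needs fixing on either reading.

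Second, surgery may be rare. Rising hCG under expectant management leads to MTX, and the Discussion says inadequate decline is handled with further injections. The power calculation assumes 40% failure in the expectant arm, so 20% operated on would mean half of all failures. That stands, and makes 20% v 5% a steep case.

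Third, surgery is compared between arms as a (re)intervention and repeat ectopic pregnancy has its own curve, so an excess of surgery would be seen. That stands too. What would not be seen is its effect on the fertility estimate.

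Fourth, the outcome-definition section may simply be the shorter statement. It omits the IVF stop as well, so the mismatch is not specific to surgery. Both stops need aligning.

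A reader might infer that failure in either arm ends in surgery. It does not: the trigger of more than four injections is written for the MTX arm only, and instability or signs of rupture are the triggers common to both.

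**Conclusion.** The point holds as a should-fix matter for a secondary outcome. Followed as written, the rule censors on a possible consequence of allocation and conflicts with the intention-to-treat principle stated in the same section. The bias in the rate ratio is towards 1 if surgery lowers spontaneous conception and its frequency differs between arms. If frequency and effect are equal, mainly the absolute probabilities are overstated.

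The size is unknown. The illustrations give about 1.5 to 1.7 points for 10% v 3% with conception halved, and about 3 to 7 points for 20% v 5% with conception halved or quartered. They rest entirely on assumed surgery and conception rates and on surgery falling early. With 72 women the effect is probably small relative to sampling error.

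A reader might go further and conclude that the trial would conceal a real fertility harm of expectant management, or pass a known bias into the meta-analysis mentioned in the Discussion. The documents do not support this. They do not say that surgery reduces fertility, that it will be more frequent in the expectant arm, or that fertility will be pooled. The primary outcome and the sample size are untouched.

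**What to change.** In the Analysis section, remove the stop at tubal surgery from the main fertility analysis. State explicitly that surgery for the index pregnancy or for a repeat ectopic pregnancy does not censor. Keep every woman in her allocated arm and at risk to 24 months or last contact.

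If an estimate censored at surgery is wanted, show it as a labelled sensitivity analysis, define which operations count, and give the number operated on per arm.

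Make the end-of-follow-up rule the same in Secondary outcome measures and in Analysis, and say in both whether the start of IVF ends follow-up.

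The cost is a few sentences of analysis wording. The six-monthly questionnaires already planned for both arms ask about pregnancies and their outcomes; the added task is to make sure that conceptions after surgery are taken from them and analysed. Reported pregnancy probabilities may be slightly lower.

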### Outcome measures

#### Primary outcome measure

The primary outcome measure is an uneventful decline of serum hCG to an undetectable level (< 2 IU/l) by the initial intervention strategy, i.e. expectant management or a single dose systemic MTX.

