#### Power calculation

Assuming an uneventful decline of serum hCG of 60% in the expectant management group and of 90% in the MTX group, and assuming a power of 80% and a significance level of 5%, 36 patients in each group are needed [6,15,22-24].

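### The economic evaluation may become a cost-only comparison if the strategies appear equivalent, but a trial sized for a 30-point difference cannot reliably establish equivalence

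*Protocol article*

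**What the plan says.** The rule is one sentence in the protocol article, Analysis: "the economic evaluation will be a cost-effectiveness analysis or a cost-minimisation analysis", the choice being conditional on how far the two strategies differ or are equivalent. It names no outcome, margin or test for deciding between the two forms.

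The only comparison described there for short-term results is an estimate with an interval: "Short term outcome measures are compared by calculating relative risks and their 95% confidence intervals". The primary outcome is binary: "The primary outcome measure is an uneventful decline of serum hCG to an undetectable level (< 2 IU/l) by the initial intervention strategy".

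The Power calculation section sizes the trial to find a difference. "Assuming an uneventful decline of serum hCG of 60% in the expectant management group and of 90% in the MTX group", with 80% power and 5% significance, it concludes that "36 patients in each group are needed". The Objective asks whether expectant management can serve as an alternative to methotrexate (MTX), and costs are one of the terms in which this is judged.

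**The concern.** A cost-minimisation analysis compares costs alone. It is valid when effects are known to be equal, because it sets both the effect difference and its uncertainty to zero. A cost-effectiveness analysis keeps both. Choosing between them after the clinical result is known is safe only if the trial can tell equal effects from effects that are merely estimated imprecisely.

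This trial was designed to detect a large difference. A result that shows no clear difference may reflect equality or may reflect 36 patients per group. If the second is taken for the first, the economic conclusion could be that expectant management saves money at no loss, when the data are compatible with a material loss. Expectant management has no initial drug cost, so the cost-only comparison starts with one item in its favour.

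**Working it through.** **Inputs.** From Power calculation: 36 per group, success 60% (expectant) and 90% (MTX), power 80%, significance 5%. Sidedness is not stated; two-sided is assumed. No equivalence margin is given, so margins of 5, 10, 15 and 20 points are assumed, with both true rates at the protocol's 90%.

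**1. The protocol's own figure.** With mean rate 0.75,

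n = [1.960 × √(2 × 0.75 × 0.25) + 0.842 × √(0.6 × 0.4 + 0.9 × 0.1)]² / 0.30² = (1.200 + 0.483)² / 0.09 ≈ 31.5, so 32 per group.

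With continuity correction it is 38. Exact enumeration with a two-sided Fisher test at 36 per group gives 80.0% power. The stated 36 is thus reproduced as a sample size for detecting a difference, and it is not in error.

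**2. Power to show equivalence at 36 per group** (two one-sided tests, normal approximation).

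SE of the difference = √(2 × 0.9 × 0.1 / 36) = √0.005 = 0.0707

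Power = 2Φ(margin/SE − z) − 1, set to 0 if negative, with z = 1.960 (one-sided 2.5%) or 1.645 (one-sided 5%)

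Needed per group for 80% power = 0.18 × (z + 1.282)² / margin²

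| Margin (points) | margin/SE | Power, 2.5% | Power, 5% | Needed per group, 2.5% / 5% |
|---|---|---|---|---|
| 5 | 0.707 | 0% | 0% | 757 / 617 |
| 10 | 1.414 | 0% | 0% | 190 / 155 |
| 15 | 2.121 | 13% | 37% | 85 / 69 |
| 20 | 2.828 | 61% | 76% | 48 / 39 |

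For example, at 20 points and 2.5%: 2Φ(2.828 − 1.960) − 1 = 2Φ(0.868) − 1 = 0.615. The zeros come from the approximation and are best read as about zero. The 95% interval explains them: its half-width is 1.96 × 0.0707 = 13.9 points, wider than a 10-point margin even when the observed difference is nil.

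**3. How often a true loss would lead to the cost-only analysis.** The trigger is not stated, so two are tried. Each cell sums the binomial probabilities of all outcome pairs (a of 36, b of 36) that meet the trigger. In trigger A the 95% interval for the relative risk, exp{ln(a/b) ± 1.96 √(1/a − 1/36 + 1/b − 1/36)}, includes 1. In trigger B the observed difference is at most 10 points.

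| True success, expectant v MTX | True loss (points) | A: non-significant relative risk | B: observed difference ≤ 10 points |
|---|---|---|---|
| 60% v 90% (protocol's assumption) | 30 | 14% | 2% |
| 70% v 90% | 20 | 42% | 13% |
| 75% v 90% | 15 | 61% | 27% |

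Under A with Fisher's test in place of the relative-risk interval, the figures are 20%, 53% and 71%.

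**4. One possible result.** With 27/36 v 32/36, the relative risk is 0.750/0.889 = 0.84 and the standard error of its logarithm is 0.113, so the 95% interval is 0.68 to 1.05. It includes 1, yet it allows a loss of about a third of successes. A cost-only analysis would leave that out of the economic result.

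**The case against.** Several counter-arguments have force.

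- **The trigger.** A reader might infer that a non-significant relative risk causes the switch. The document does not say so, and its phrase names neither a p-value nor an outcome. The frequencies in step 3 depend strongly on this: a 10-point rule cuts 42% to 13% and 61% to 27%.
- **The margin.** This is a condensed article, and a working definition of equivalence may stand in the full protocol or analysis plan. Its absence here is therefore not a fault. It would not remove the problem, however, because the sample size is fixed in this document.
- **Equivalence is not out of reach altogether.** A reader might infer that the trial could never show it. That is firm only for margins up to about 10 to 15 points. At 20 points, equivalence power is 61% to 76%, and power for one-sided non-inferiority (one-sided 2.5%) is 81%.
- **A loss of effect would not vanish entirely.** Under Follow up, inadequate hCG decline or rupture leads to further MTX or surgery, and costs are built from resources used. Much of a lower success rate would therefore reach the cost comparison. Its consequences for health and quality of life would not. The relative risk and its interval are reported whichever economic form is chosen.

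What survives is narrower: a result-dependent rule is printed, and the printed design cannot reliably meet its condition.

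**Conclusion.** The point holds in a limited form. The plan allows the effect side of the economic evaluation to be dropped on a finding of equivalence, and 36 per group gives little or no power for such a finding at margins up to 15 points and less than 80% at 20. A real but imprecise loss could then be treated as zero on the effect side, with rescue costs still counted. It would go too far to say that this must happen.

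The power figures assume both true rates are 90%, and the margins are assumptions. How often a switch would occur is uncertain: 42% or 13% for a true 20-point loss, depending on the trigger. Under the protocol's own 60% v 90% it would be uncommon under either trigger (14% or 2%). The primary analysis, the sample size and the data collected are unaffected. This is a minor point on a secondary outcome.

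**What to change.** In the Analysis section, delete the condition. State that a cost-effectiveness analysis will be performed whatever the clinical result, with uncertainty in patient-level costs and effects handled jointly and the cost difference shown as one component. The choice of effect measure and the form of presentation can be left to the analysis plan.

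The cost is one sentence; no extra patients or data are needed. There is one small downside: the incremental ratio may be unstable when the effect difference is near zero, so the joint uncertainty should be reported and not the ratio alone.

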#### Power calculation

Assuming an uneventful decline of serum hCG of 60% in the expectant management group and of 90% in the MTX group, and assuming a power of 80% and a significance level of 5%, 36 patients in each group are needed [6,15,22-24].

## Discussion

About 10% of women presenting with suspected EP, are diagnosed with a visible EP but with low and plateauing serum hCG concentrations or a persisting PUL [24]. Thus far, these particular subgroups of women are offered medical treatment with MTX based on the proven effectiveness of systemic MTX in women with selected EPs [12,16,19]. The question is whether it is really necessary to treat these women at all. This RCT will provide evidence whether expectant management is an alternative to systemic MTX in a single dose im regimen in women with an EP with low but plateauing serum hCG concentrations or persisting PUL.

Simultaneously with our trial, another trial is ongoing in the United Kingdom [20]. This placebo controlled trial has a similar objective, uses the same inclusion criteria and interventions (single shot MTX im and expectant management). In the UK trial, however, surgical intervention is installed in both treatment groups if inadequately declining serum hCG concentrations occur after one week of follow up. In our study, these treatment failures are treated with additional MTX injections. In the near future, meta analysis of the results of both trials will provide guidance on the present management dilemmas in women with EP or PUL with low and plateauing serum hCG concentrations.
